#### 2.2.6 Management of Adverse Events

2.4.1

1.Records and reportsThe investigator should explain to the patient that they (or a family member) should accurately report all physical changes after treatment. The doctor should avoid leading questions and observe the adverse reactions when observing the effects. Whether adverse effects or adverse events are associated with the treatment methods in this study, they should be detailed in the record, including adverse reaction times, symptoms, physical signs, adverse reaction degrees, adverse reaction durations, laboratory examination indices, treatment methods, and results and follow-up times.If serious adverse events occur during the course of treatment, the investigator must report the adverse events to the clinical research department within 20 hours or no later than the second working day. The investigator will sign and date the report. The investigator should record when, how and to whom they reported the serious adverse events in the original data.2.Treatment of patientsIn cases of adverse events, the investigator may take necessary measures according to the condition of the disease until the situation is stable. Patients with abnormal test results should be tracked until the results return to normal. The investigator will decide whether to end the observation. The follow-up method can be selected according to the degree of adverse events, including hospitalization, outpatient observation, home visit, telephone call, and communication.

### 3 Interventions

2.5

#### Grouping and acupoint selection

2.5.1

1.Single acupoint group: Shenmen (HT7).2.Compatibility acupoint group: Shenmen (HT7), Baihui (DU20), Sanyinjiao (SP6).3.Control group: nonacupoint.

#### Acupoint locations and treatment

2.5.2

The locations of points in the single acupoint and compatibility acupoint groups will be referenced using the national standard of the People's Republic of China in 2006 (GB/T 12346–2006) in the following form: “The name and location of Acupoint ." The acupuncture will be applied based on “Acupuncture and Moxibustion,” edited by Liang Guangsheng, the Ministry of Health's 12th five-year plan.

Shenmen (HT7) is located on the anteromedial aspect of the wrist, radial to the flexor carpi ulnaris tendon, on the palmar crease and should be punctured perpendicularly 0.3 to 0.5 cun. Sanyinjiao (SP6) is on the tibial aspect of the leg, posterior to the medial border of the tibia, and 3 cun superior to the prominence of the medial malleolus, and it should be punctured perpendicularly 1.0 to 1.5 cun. Baihui (DU20) is located on the head, 5 cun directly above the midpoint of the anterior hairline, at the midpoint of the line connecting the apexes of both ears, and it should be punctured transversely 0.5 to 1.0 cun. The nonacupoint is in the medial arm on the anterior border of the insertion of the deltoid muscle at the junction of the deltoid and biceps muscles and is punctured perpendicularly 2 mm.

HT7, SP6, and DU20 require lifting and thrusting, combined with twirling and rotating, of the needles to achieve the DeQi sensation, and the needles will be retained for 30 minutes. The nonacupoint patients will not be asked about the DeQi sensation or any manipulation.

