## Abstract

**Background::**

Acupuncture may be a clinically effective treatment for insomnia. We will perform a multicenter, large-scale, single-blinded, randomized controlled trial to compare the differences in the clinical efficacy between the use of singleacupoints and compatibilityacupoints in the treatment of primary insomnia.

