**Figure 2 (Continued) F3:**
[figure not shown]
Trial process chart.

The total observation period of this trial will be 10 weeks. All patients will be followed for 1 week before randomization (baseline phase). After randomization, the patients will receive 30 minutes of electroacupuncture once per day for 5 weeks. In the fourth week after the treatment, follow-up will be performed 1 time.

The single-blind evaluation method will be used in this trial. Nevertheless, the patients will be informed that they will be in either one of the acupoint treatment groups or the nonacupoint control group, which is the most effective way to avoid bias.

To communicate in a timely manner between each subcenter and to improve the efficiency of the trial, central randomization will be used, as performed by the China Academy of Traditional Chinese Medicine clinical evaluation center. The patients will be registered in the groups by phone or network at any time and any geographic location, such that the test manager can monitor the progress of each subcenter subject in real time.

This trial will be performed according to the principles of the Declaration of Helsinki (Version Edinburgh 2000). The trial protocol has been approved by the local institutional review board and ethics committee. Written informed consent will be requested from all participants before registration. All patients will be given enough time to decide whether they should sign the informed consent form, and they will be given treatment options other than acupuncture if they are not willing to participate.

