#### Outcome measurement

2.7.1

The primary outcome measure in this trial will be the PSQI, and the secondary outcome measures will include the sleep diary, Athens insomnia scale score, SF-36 score, ET results, and PSG results.

PSQI^[16,17]^ is a self-rated questionnaire that assesses sleep quality and disturbances over a 1-month time period. Nineteen individual items generate 7 “component” scores: subjective sleep quality, sleep latency, sleep duration, habitual sleep efficiency, sleep disturbances, use of sleeping medication, and daytime dysfunction. The sum of scores for these 7 components yields 1 global score. All patients will complete the PSQI 1 week before randomization and in the fifth and eighth weeks after randomization.

The sleep diary^[18]^ will be used to record the patients’ sleep and to collect sleep information to assess the therapeutic effect after treatment. Patients will need to complete the sleep diary every day during the treatment period and complete the CRFs only once a week.

The Athens insomnia scale will be used to record the patients’ self-assessment of sleep disorders. The items include sleep latency, waking up at night, waking up earlier than expected, total sleep time, sleep quality, emotions during the day, physical functioning during the day and daytime sleepiness. Patients will need to complete the Athens insomnia scale 1 week before randomization and at the fifth and the ninth week after randomization.

The SF-36^[19]^ questionnaire consists of 36 items containing 8 subscales each. These subscales consist of 2 higher-level summary scales, namely, the physical (physical function, physical role function, bodily pain, and general health) and psychological (vitality, social function, emotional role function, and mental health) summary scales. Patients will complete the SF-36 1 week before randomization and at the fifth and ninth week after randomization.

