ET is a pioneering analysis technology in China that provides noninvasive, quantitative detection of the neurotransmitters involved in brain activity and brain function regardless of physiological or pathological condition. It can be applied to the study of brain function, providing objective mathematical evidence for the study of neuropsychiatric diseases and clinical treatment guidance. Patients will need to perform ET 1 week before randomization and at the third and fifth weeks after randomization. Patients will also need to undergo PSG 1 week before randomization and at the fifth week after randomization.

Biological indicators, including body temperature, heart rate, respiration and blood pressure, will be measured 1 week before randomization and at the fifth and ninth weeks after randomization. Sex, age, culture, occupation, height, weight, and acupuncture expectation will also need to be recorded.

Any adverse events and the manner in which they are addressed will be recorded during the 4 treatment weeks and the 12 follow-up weeks. These adverse events include bleeding, hematoma, fainting, serious pain, and local infection. If patients suffer any serious adverse events, all details will be documented. The patients’ blood, urine, stool, liver function, renal function, and electrocardiogram analysis results will be recorded 1 week before randomization and at the fifth week after randomization.

Drop-outs, withdrawals, and patient compliance will be recorded during the treatment weeks and the 4 follow-up weeks. All patients will be recorded until the end of the trial.

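### An arm-specific DeQi rule, contradicted by the operating procedure, can cue patients who self-rate the primary outcome to their arm, in a single-blind trial that does not say who is blinded

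*Protocol article*

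**What the plan says.** **Blinding.** The abstract says "We will perform a multicenter, large-scale, single-blinded, randomized controlled trial". Section 2.1 (Design) says "The single-blind evaluation method will be used in this trial". Neither place names the blinded party. Section 2.1 goes on to say that "the patients will be informed that they will be in either one of the acupoint treatment groups or the nonacupoint control group", and presents this as the best protection against bias.

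**Outcome.** Under section 2.7.1, "The primary outcome measure in this trial will be the PSQI", and this instrument "is a self-rated questionnaire that assesses sleep quality and disturbances over a 1-month time period". The Athens scale is also described as self-assessment, and patients complete the SF-36 and the sleep diary.

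**Needling and DeQi, section 2.5.2.** "HT7, SP6, and DU20 require lifting and thrusting, combined with twirling and rotating, of the needles to achieve the DeQi sensation". For the control, the text gives a needle depth of 2 mm and then "The nonacupoint patients will not be asked about the DeQi sensation or any manipulation".

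**Needling and DeQi, section 2.6.** The standard operating procedure expects needles at sham points and real points alike to be twirled, with deqi carried out at the same time. Auxiliary needles, electrical stimulation and 30 minutes of retention apply in every arm. Treatment is given 25 times over 5 weeks.

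**Expectation.** Section 2.7.1 says that "acupuncture expectation will also need to be recorded".

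**The concern.** When the patient is the rater, a blinded evaluator protects nothing; only the patient's own ignorance of the allocation does. Section 2.5.2 makes the exchange between operator and patient depend on the arm. Patients have been told that a nonacupoint control exists, and the difference recurs at every session, so some may work out which kind of needling they are receiving. Patients who believe they are controls may report worse sleep, and those who believe they have real acupuncture may report better sleep.

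The contrast at stake is the first aim in the Introduction: whether acupuncture works, judged against the nonacupoint control. A bias of this kind pushes that contrast toward benefit, and a larger sample does not reduce it.

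The conflict between sections 2.5.2 and 2.6 adds a second problem. Six hospitals will train operators from this text, and they could deliver the control differently from one another.

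**Working it through.** The plan gives no figure on blinding, so there is none to reproduce. The check is mainly a comparison of texts.

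**Step 1. Who is blinded?** Two readings are open.
- Patients are blinded: section 2.5.2 then gives them a cue to their arm.
- Only an evaluator is blinded: the self-rated PSQI then has no blinding protection at all.

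The primary outcome is exposed on either reading.

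**Step 2. What do the two sections say about the control?**

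| Item | Section 2.5.2 | Section 2.6 |
|---|---|---|
| Manipulation | Named for HT7, SP6 and DU20 only | Sham and real points both twirled |
| DeQi | Sought at the acupoints; controls not asked | Carried out at both kinds of point |
| Asking controls about sensation | Ruled out | Not addressed |

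The first two rows conflict. The third does not: nothing in section 2.6 cancels the rule against asking controls, so the dialogue still differs even if section 2.6 governs technique. The control sentence in 2.5.2 can also be read two ways, as no question about manipulation or as no manipulation.

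**Step 3. Which comparison is affected?** Both acupoint arms are manipulated to DeQi. The cue separates acupoint from nonacupoint patients, not single from compatibility acupoints.

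**Step 4. How large could the effect be?** The documents do not say. The following is illustration by assumption.

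Inputs from section 2.8: control responders p2 = 0.25; 111 per group; 20% dropout, so 111 × 0.80 = 88.8, taken as 88. Whether the printed sample-size formula yields 111 is a separate matter. Assumed: no specific effect of acupuncture, expectation alone raises acupoint response by d, two-sided alpha 0.05.

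With p1 = 0.25 + d and p̄ = (p1 + p2)/2, the chance of a significant result favouring the acupoint arm is

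Φ{ [d − 1.96·√(2p̄(1−p̄)/n)] / √([p1(1−p1) + p2(1−p2)]/n) }.

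For d = 0.10 and n = 111: p̄ = 0.30, √(0.42/111) = 0.0615, √(0.415/111) = 0.0611. Then (0.10 − 1.96 × 0.0615)/0.0611 = −0.34, which gives 37%.

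| d (percentage points) | p1 | n = 88 | n = 111 |
|---|---|---|---|
| 5 | 30% | 11% | 13% |
| 10 | 35% | 30% | 37% |
| 15 | 40% | 57% | 67% |
| 20 | 45% | 80% | 88% |

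Without bias the figure in this direction would be 2.5%.

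On the PSQI scale, the false difference equals the shift from believing one has real acupuncture, times the gap between arms in the share who believe it. If the shift is 1 to 2 points and the gap 0.50, this is 0.5 to 1.0 point. Both inputs are assumed; the result scales with the gap and is zero if there is none.

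**The case against.** Much is shared across arms: every patient has penetrating needles, auxiliary needles, electrical stimulation, 30 minutes of retention and 25 sessions. A control patient does not see what others are asked. This stands, and it limits the claim to a cue that can unblind some patients.

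A reader might infer more than the text supports:

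- *That the dialogue reveals allocation.* Nothing says that patients are told what a question about DeQi would mean, or that they would notice its absence.
- *That operators are stated to question acupoint patients.* This is implied, because controls are singled out as those not to be asked, but it is not written.
- *That a patient blind is promised.* The article leaves the blinded party unnamed.
- *That telling patients about the control arm is itself a fault.* It is an ordinary part of informed consent. It matters only because the procedure then differs by arm.
- *That expectation has no route into the analysis.* Section 2.9.2 lets factors that materially change the effect enter as covariates. Expectation is not named there, but it is not shut out.
- *That a check of the blind is missing.* An article may leave this to the full protocol or analysis plan, so its absence is no fault here.
- *That nothing in the trial could show the bias.* Polysomnography, a secondary outcome, is not self-reported and offers a partial cross-check.

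It can also be said that section 2.6 removes the difference between arms. It does so only for technique and only if it governs. The rule against asking controls remains.

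**Conclusion.** The point holds as a defect in what is written: an arm-specific rule on DeQi, contradicted in part by the operating procedure, in a trial with a self-rated primary outcome and an unnamed blinded party. If section 2.5.2 is followed, patients can be cued to their allocation, and the acupoint-versus-nonacupoint PSQI comparison can be biased toward benefit. The comparison of single with compatibility acupoints is not affected by this cue.

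The size is unknown. The figures above rest on assumed expectation effects and show only that a moderate one could produce a positive result. The conclusion assumes that some patients notice the difference in dialogue or handling and that belief about allocation influences self-rating. The article neither establishes nor excludes this.

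**What to change.** 1. In section 2.1, say who is blinded, and state that it is the patients if that is what is intended.
2. Reconcile sections 2.5.2 and 2.6 on manipulation and DeQi in the control arm, so that all six hospitals train from one text. Which technique is right is for the investigators to settle.
3. Replace the arm-specific asking rule in section 2.5.2 with one fixed operator script for all three arms: the same sensation question at the same moments, with the answer recorded whatever it is.

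Optional additions are a guess-the-group question with its reason (for example in the first treatment week and at week 5), and a supportive PSQI analysis adjusted for the recorded baseline expectation. That adjustment cannot repair unblinding that arises after randomization.

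The cost is script wording and operator training, plus one or two questions and one supportive analysis if the options are taken. There is a small downside: controls would be asked about a sensation that may not be sought, which could itself act as a cue. A common script also leaves any differences in needling depth or manipulation in place.

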#### Needles

2.5.3

The needles are 25 mm in length and 0.25 mm in diameter or50 mm in length and 0.30 mm in diameter. The needles that are 13 mm in length and 0.18 mm in diameter will be used as auxiliary needles and will not be manipulated.

The sterile acupuncture needles used in this trial, namely, Hwato needles, made by Suzhou Medical Supplies Factory in China, are for single use.

### Operating physician

2.6

The physicians who will participate in this trial will be required to pass training in standard clinical operating procedures.

SOP for the basic operation of acupuncture:

1.DisinfectionDisinfection of the doctor's hands: Before acupuncture, the doctors will wash their hands with soap and water and then wipe their hands with 75% alcohol swabs before holding the needles.Disinfection of the acupuncture site: The local skin at the acupuncture site will be wiped and sterilized with 75% alcohol cotton balls, and a ring will be sterilized from the center to the surroundings.2.NeedlingUsing the 2-handed approach, according to the characteristics of the location of the acupuncture points, which will be used to select the claw cutting or clamping method, the direction and depth of acupuncture will be in strict accordance with the requirements of acupuncture operation.3.Retention of the needlesWe expect that the sham acupuncture points and the needle points will be plugged and twirled, and “deqi”will be performed simultaneously. All needles will be left in place for 30 minutes and will not be removed during the needle retention process.4.Needle removalWith the left thumb and index finger holding the sterile dry cotton ball gently pressed on the acupuncture site, holding the needle in the right hand for slight twisting, the practitioner will slowly bring the needle to the skin, let it rest for a moment, and then take the needle out, pressing the pinhole to prevent bleeding.5.The electroacupuncture operationAfter each acupoint or nonacupoint is needled, auxiliary needles will be used for puncture at locations 2 mm lateral to every acupoint or nonacupoint to a depth of 2 mm without manual stimulation. After needle insertion, transcutaneous electric acupoint stimulation (HAMS: Han's acupoint nerve stimulator, HANS-200, Nanjing, China) will be used for electroacupuncture stimulation at every acupoint or nonacupoint.Each acupuncture needle used for acupoints or nonacupoints and their auxiliary needles will be connected to electricity by the HANS for 30 minutes. The stimulation frequency will be 60/100 Hz, and the stimulation intensity will vary from 0.1 to 1.0 mA until the patients feel comfortable.6.Treatment courseAll patients will receive 25 treatments over a period of 5 weeks, once a day, 5 times consecutively with 2-day breaks every week. Follow-up will be performed in the fourth week after treatment.

### Statistical analysis

2.7

#### Outcome measurement

2.7.1

The primary outcome measure in this trial will be the PSQI, and the secondary outcome measures will include the sleep diary, Athens insomnia scale score, SF-36 score, ET results, and PSG results.

PSQI^[16,17]^ is a self-rated questionnaire that assesses sleep quality and disturbances over a 1-month time period. Nineteen individual items generate 7 “component” scores: subjective sleep quality, sleep latency, sleep duration, habitual sleep efficiency, sleep disturbances, use of sleeping medication, and daytime dysfunction. The sum of scores for these 7 components yields 1 global score. All patients will complete the PSQI 1 week before randomization and in the fifth and eighth weeks after randomization.

The sleep diary^[18]^ will be used to record the patients’ sleep and to collect sleep information to assess the therapeutic effect after treatment. Patients will need to complete the sleep diary every day during the treatment period and complete the CRFs only once a week.

The Athens insomnia scale will be used to record the patients’ self-assessment of sleep disorders. The items include sleep latency, waking up at night, waking up earlier than expected, total sleep time, sleep quality, emotions during the day, physical functioning during the day and daytime sleepiness. Patients will need to complete the Athens insomnia scale 1 week before randomization and at the fifth and the ninth week after randomization.

The SF-36^[19]^ questionnaire consists of 36 items containing 8 subscales each. These subscales consist of 2 higher-level summary scales, namely, the physical (physical function, physical role function, bodily pain, and general health) and psychological (vitality, social function, emotional role function, and mental health) summary scales. Patients will complete the SF-36 1 week before randomization and at the fifth and ninth week after randomization.

ET is a pioneering analysis technology in China that provides noninvasive, quantitative detection of the neurotransmitters involved in brain activity and brain function regardless of physiological or pathological condition. It can be applied to the study of brain function, providing objective mathematical evidence for the study of neuropsychiatric diseases and clinical treatment guidance. Patients will need to perform ET 1 week before randomization and at the third and fifth weeks after randomization. Patients will also need to undergo PSG 1 week before randomization and at the fifth week after randomization.

Biological indicators, including body temperature, heart rate, respiration and blood pressure, will be measured 1 week before randomization and at the fifth and ninth weeks after randomization. Sex, age, culture, occupation, height, weight, and acupuncture expectation will also need to be recorded.

Any adverse events and the manner in which they are addressed will be recorded during the 4 treatment weeks and the 12 follow-up weeks. These adverse events include bleeding, hematoma, fainting, serious pain, and local infection. If patients suffer any serious adverse events, all details will be documented. The patients’ blood, urine, stool, liver function, renal function, and electrocardiogram analysis results will be recorded 1 week before randomization and at the fifth week after randomization.

Drop-outs, withdrawals, and patient compliance will be recorded during the treatment weeks and the 4 follow-up weeks. All patients will be recorded until the end of the trial.

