**Methods/Design::**

A total of 333 participants will be randomly assigned to 2 acupoint treatment groups or 1 nonacupoint control group in a 1:1:1 ratio by a central stochastic system. The acupuncture groups are: the single acupoint group: Shenmen (HT7); and he compatibility acupoint group: Shenmen (HT7), Baihui (DU20), and Sanyinjiao (SP6). The observation period of this trial will be 10 weeks. All patients will be followed for 1 week before randomization (baseline phase). After randomization, the patients will receive 30 minutes of electro-acupuncture once per day for 5 weeks. In the fourth week after the treatment, follow-up will be performed once. The primary outcome will be the Pittsburgh sleep quality index score at 1 week before randomization and 2 and 8 weeks after randomization. The secondary outcomes will include data from sleep diaries, Athens insomnia scale scores, ShortForm-36 Health Survey scores, electroencephalogram technology results and polysomnogram) results. Patients will be required to complete a sleep diary every day during the treatment period. Patients will also undergo electroencephalogram technology and polysomnogram 1 week before randomization and 5 weeks after randomization. The other secondary outcomes will be measured 1 week before randomization and 5 and 9 weeks after randomization.

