#### Validity analysis

2.9.1

The efficacy scores for week 0, week 2, and week 4 for patients with primary insomnia will be calculated using the difference between the treatment period and baseline period. These indicators will be described by mean, standard deviation, median, P5, P75, and maximum and minimum values. PP and ITT will be used to analyze the main indicators and overall indicators. Because this study is a multicenter randomized controlled clinical trial, the central effect on the therapeutic effect will be considered in the analysis.

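### The primary PSQI outcome has two incompatible assessment schedules (weeks 2 and 8; weeks 5 and 8), and the efficacy analysis at weeks 0, 2 and 4 matches neither

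*Protocol article*

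**What the plan says.** The abstract (Methods/Design) states: "The primary outcome will be the Pittsburgh sleep quality index score at 1 week before randomization and 2 and 8 weeks after randomization". Section 2.7.1 (Outcome measurement) states: "All patients will complete the PSQI 1 week before randomization and in the fifth and eighth weeks after randomization". Both concern the PSQI as primary outcome, and they disagree on the first post-baseline assessment.

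Section 2.9.1 (Validity analysis) sets the analysis times: "The efficacy scores for week 0, week 2, and week 4 for patients with primary insomnia will be calculated". The scores are formed "using the difference between the treatment period and baseline period". The section does not name the PSQI, but its scope includes the primary outcome: "PP and ITT will be used to analyze the main indicators and overall indicators".

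On the calendar, treatment lasts 5 weeks. Section 2.6 (treatment course) says "Follow-up will be performed in the fourth week after treatment", and the Design section says the same: "In the fourth week after the treatment, follow-up will be performed 1 time". The Athens scale, the SF-36 and vital signs are all scheduled at weeks 5 and 9 after randomization.

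Section 2.7.1 also says that the PSQI "is a self-rated questionnaire that assesses sleep quality and disturbances over a 1-month time period".

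**The concern.** The first post-baseline PSQI falls either in mid-treatment (week 2) or at the end of treatment (week 5). These are different quantities, and no reading makes both statements true. The analysis section then asks for scores at weeks that section 2.7.1 does not collect. Counted from randomization, it also leaves out the end-of-treatment score.

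Two things are at stake. The first is data collection: a site that follows the wrong passage will miss an assessment that cannot be recovered. The second is the confirmatory claim: with more than one candidate week and no primary week named, the reported result could depend on which week is presented.

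**Working it through.** **1. Calendar.** The stated total observation period is 10 weeks. It reproduces as 1 baseline week + 5 treatment weeks + 4 weeks to follow-up = 10. Follow-up is therefore at 5 + 4 = week 9 after randomization. The fourth week after treatment runs from 8 to 9 elapsed weeks.

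**2. Schedules side by side** (post-baseline weeks after randomization).

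| Source | Weeks | Shared with abstract | Shared with 2.7.1 |
|---|---|---|---|
| Abstract | 2, 8 | – | 8 |
| 2.7.1 | 5, 8 | 8 | – |
| 2.9.1, counted from randomization | 2, 4 (week 0 is baseline) | 2 | none |
| 2.9.1, counted from end of treatment | 5, 7, 9 | none | 5 |

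Neither way of counting reconciles 2.9.1 with either PSQI schedule. Under the 2.7.1 schedule, the analysis asks for weeks without a PSQI: weeks 2 and 4 on one count, weeks 7 and 9 on the other.

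**3. Recall window.** Take the 1-month recall as 4 weeks and treatment as running from 0 to 5 weeks. For a score at t weeks, the treated part of the window is min(t, 5) − max(t − 4, 0), not below zero.

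- t = 2: 2 − 0 = 2 weeks treated, 2 weeks before treatment.
- t = 4: 4 − 0 = 4 weeks treated.
- t = 5: 5 − 1 = 4 weeks treated.
- t = 8: 5 − 4 = 1 week treated, 3 weeks after treatment.
- t = 9: 5 − 5 = 0 weeks treated.

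If a month is taken as 30 days, the window at 9 full weeks opens on day 63 − 30 = 33. That is 2 days before treatment ends on day 35, so week-9 recall is almost entirely post-treatment but not strictly so. For a visit at the start of the follow-up week (8 elapsed weeks), the overlap is 1 week.

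**4. Cost of choosing a week.** Consider one between-group contrast, tested two-sided at 0.05 at each of two weeks, with the better result reported. If the two tests are independent, the error is 1 − 0.95² = 0.0975. The document gives no between-week correlation, so a range was simulated (400,000 draws): 9.1% at 0.5, 8.4% at 0.7 and 7.8% at 0.8. The range is about 8–10%, against 5% with one named week.

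**The case against.** Several stronger readings are tempting, and the document does not support them.

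- **Three conflicting PSQI timings.** Only two passages name the PSQI. Section 2.9.1 speaks of efficacy scores, and the daily sleep diary could supply weeks 2 and 4. Reading the PSQI into 2.9.1 is fair, because the section covers the main indicators, but it is an inference.
- **No visit at week 8.** The process chart is not shown. Eight elapsed weeks is the start of the fourth week after treatment. What can be said is that the PSQI carries a different week label from every other scale taken at follow-up.
- **A family-wise error near 20%.** Three pairwise contrasts at two times, all unadjusted, simulate to 21.3% and 19.6% at between-week correlations of 0.5 and 0.7. The three contrasts at a single time already give 12.2%. Most of that error comes from having three arms and would remain after the timing is fixed.
- **Four times the patients at week 2.** This needs even averaging over the recall period and an immediate full effect, and it applies only to the abstract's schedule. The document gives no PSQI effect size or time course, so the figure is not used here.
- **The result will be chosen after the data are seen.** This is a risk, not something shown. A statistical analysis plan that is not at hand may name one primary week.

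The last objection does not remove the point. An analysis plan naming one week would still leave passages of this document in contradiction. Nor is a slip in the abstract enough to explain it: correcting the abstract leaves the mismatch between 2.7.1 and 2.9.1 and the different follow-up labels.

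**Conclusion.** The point holds as a contradiction about when the primary outcome is collected and analysed. The abstract and 2.7.1 conflict outright on week 2 versus week 5. The analysis times in 2.9.1 fit neither schedule on either count. That the omission of the end-of-treatment score follows only when weeks are counted from randomization does not change this. The follow-up PSQI label differs by one week from the other scales.

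The size attributable to timing is about 8–10% false-positive error per contrast instead of 5%, if the better of two weeks is reported. This rests on an assumed between-week correlation of 0 to 0.8. The recall argument rests on a 4-week window. It shows that the choice of week changes what is estimated, but it does not give a size for the change in effect. The matter should be settled before unblinding, because it concerns the primary endpoint.

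**What to change.** Reconcile the abstract, 2.7.1 and 2.9.1, and name one primary time point before unblinding. The natural choice is the PSQI global score at week 5, compared with baseline: it marks the end of treatment, is already scheduled in 2.7.1, and its recall window lies within treatment. Another week could be defended, provided that only one is named.

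Take the follow-up PSQI with the other scales at the existing week-9 follow-up, and make it a secondary endpoint. Placing it towards the end of that week keeps the recall almost entirely post-treatment. In 2.9.1, replace weeks 0, 2 and 4 with baseline, week 5 and week 9, say that weeks count from randomization, and name the PSQI. Align the abstract.

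The cost is wording in three places and one questionnaire moved to a follow-up that already exists. No extra visit or patients are needed.
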